# SUBJECT POPULATION

## Number of Subjects and Subject Selection

Thirty (30) subjects will be enrolled in this study.

At this time, thirty subjects have been successfully enrolled. There is enough study drug left to enroll one more subject in this study. Since there is enough study drug to treat someone, an extra study subject will be enrolled and will follow the same protocol guidelines as the previous subjects.

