## Exclusion Criteria

Subjects who meet *any* of the following exclusion criteria are not to be enrolled in this study.

**(1)** HIV+;

**(2)** HBV surface antigen +;

**(3)** Non-definitive HCV genotype results;

**(4)** Previously received treatment for HCV (interferon, ribavirin, or DAA);

**(5)** Taking medications that affect pharmacokinetics of LDV/SOF (proton-pump inhibitors, anticonvulsants [phenobarbital, phenytoin, carbamazepine, oxycarbazepine], rifamycins, rosuvastatin, herbs [St. John’s wort, silymarin, echinacea]);

**(6)** History of any of the following:

- 1. Current gastrointestinal disorder or post-operative condition that could interfere with the absorption of the study drug
  2. History of hepatic decompensation (i.e., ascites, encephalopathy or variceal hemorrhage)
  3. History of solid organ or bone marrow transplantation
  4. Current treatment for cancer

**(7)** Chronic liver disease for non‑HCV reason (e.g., Wilson’s disease, alpha‑1 antitrypsin deficiency, cholangitis) except iron overload;

**(8)** Use of any prohibited concomitant medications as described in Section 5.2 within 21 days of the enrollment visit; and

**(9)** Known hypersensitivity to LDV, SOF, the metabolites, or formulation excipients.

**(10)** Any other conditions that preclude study involvement as determined by PI.

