## Prior and Concomitant Medications

Concomitant medications taken within 30 days prior to screening will be recorded in the source documents and case report form(s) (CRFs).

Concomitant use of certain medications or herbal/natural supplements (inhibitors or inducers of drug transporters i.e., P‑gp) with study drug may result in PK interactions increasing or decreasing exposure to study drug.  Examples of representative medications which are prohibited from 21 days prior to enrollment through the end of treatment are listed below. The use of amiodarone is prohibited from **60 days prior to enrollment** through the end of treatment. Participants will be advised to avoid selected medications until 21 days after the end of treatment (e.g. digoxin and rosuvastatin)

Table 5‑1. Concomitant Medications Disallowed or to be used with Caution

| Drug Class | Agents Disallowed | Use with Caution |
| --- | --- | --- |
| Acid Reducing Agents^a^ |  | Proton- Pump Inhibitors, H2‑Receptor Antagonists, Antacids |
| Anticonvulsants^b^ | Phenobarbital, Phenytoin, Carbamazepine, Oxcarbazepine |  |
| Antimycobacterials^b^ | Rifabutin, Rifapentine, Rifampin |  |
| Cardiac Medications | Amiodarone^c^ | Digoxin^d^ |
| Herbal/Natural Supplements^b^ | St. John’s Wort, Echinaccea, Milk thistle (i.e., silymarin), Chinese herb sho-saiko-to (or Xiao-Shai-Hu-Tang) |  |
| HMG-CoA Reductase Inhibitors^e^ | Rosuvastatin |  |

a It is recommended to separate antacid and LDV/SOF administration by 4 hours. H2-receptor antagonists may be administered simultaneously with or staggered from LDV/SOF at a dose that does not exceed doses comparable to famotidine 40 mg twice daily. Proton-pump inhibitor doses comparable to omeprazole 20 mg can be administered simultaneously with LDV/SOF. Proton-pump inhibitors should not be taken before LDV/SOF.

b May result in a decrease in the concentrations of study drug.

c May result in symptomatic bradycardia. Mechanism is not currently known. The use of amiodarone is prohibited from 60 days prior to Baseline/Day 1 through the end of treatment.

d May result in an increase in the concentration of study drug and/or concomitant medications. Co-administration of LDV/SOF with digoxin may increase the concentration of digoxin. Caution is warranted and therapeutic concentration monitoring of digoxin is recommended when co-administered with LDV/SOF.

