## Pretreatment Assessments

### Screening Visits

Subjects will be screened within 30 days of enrollment to determine eligibility for participation in the study. The screening window can be extended to 42 days in exceptional circumstances. Subjects meeting all of the inclusion criteria and none of the exclusion criteria will return to the clinic within 30 days after screening for enrollment into the study.

After consent is obtained and eligibility is determined, screening assessments (split between two visits) will include medical history and physical examination (including weight and height), review of systems, vital signs, concomitant medications, CBC with diff/CMP, PT/INR, HBsAg, HCV RNA, HCV genotype and sub-type (or lab documentation during period of diagnosis of chronic HCV), urine drug screen, HIV Ag/Ab test, and stored sample for potential HCV sequence analysis.

Subjects will be compensated $15 for screen 1 and $15 for screen 2.

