### Medical History

Medical history including details regarding illnesses and allergies, date(s) of onset, and whether condition(s) is currently ongoing, and medication history will be collected on all subjects during screening.

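### Exclusion (8) gives every prohibited drug a 21-day look-back, but Section 5.2 prohibits amiodarone from 60 days before enrollment

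*Protocol*

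**What the plan says.** Section 4.3, exclusion (8), bars "Use of any prohibited concomitant medications as described in Section 5.2 within 21 days of the enrollment visit". It names no drugs. It relies on Section 5.2 for the list and states its own time limit.

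Section 5.2 has two limits. Its general sentence introduces example drugs that are "prohibited from 21 days prior to enrollment through the end of treatment are listed below". The next sentence gives amiodarone a separate 60-day limit, with the period in bold. Table 5-1 places amiodarone among the disallowed agents, and footnote c repeats the rule: "The use of amiodarone is prohibited from 60 days prior to Baseline/Day 1 through the end of treatment". The same footnote gives symptomatic bradycardia, of unknown mechanism, as the hazard.

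Three other passages bear on the point:

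- Section 6.2.1 makes the eligibility list the gate to enrollment: "Subjects meeting all of the inclusion criteria and none of the exclusion criteria will return to the clinic within 30 days after screening" for enrollment.
- Section 6.10.2 says that "medication history will be collected on all subjects during screening", with no day limit.
- Section 4.1 reports that the planned thirty subjects are enrolled and that "There is enough study drug left to enroll one more subject in this study".

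**The concern.** An eligibility criterion and the section it cites give different look-back periods for the same drug, and the shorter one sits in the list that decides who enters. The longer one exists for a stated safety reason. A site that checks subjects against Section 4.3 and applies the 21 days as printed could pass someone whom Section 5.2 still bars. What is at stake is one subject's safety and a protocol deviation created by the protocol's own wording. No estimate, test or precision statement depends on it.

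**Working it through.** The protocol gives no figure to reproduce here. The check sets the two windows side by side and then looks for any other criterion that closes the gap.

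**Inputs**

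| Source | Drug | Look-back before enrollment |
| --- | --- | --- |
| Section 4.3, exclusion (8) | every drug prohibited in 5.2 | 21 days |
| Section 5.2, general sentence | listed drugs | 21 days |
| Section 5.2, next sentence, and Table 5-1 footnote c | amiodarone | 60 days |

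The body text counts from enrollment and footnote c from Baseline/Day 1. Section 6.2.2 gives the first dose or dispensation at the enrollment visit, so both are taken as the same day.

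**Gap.** Days prohibited by 5.2 minus days covered by (8): 60 − 21 = 39, namely days 22 to 60 before enrollment.

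**Other criteria.**

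- Exclusion (5) begins "Taking medications that affect pharmacokinetics of LDV/SOF". It concerns current use, and its list (proton-pump inhibitors, anticonvulsants, rifamycins, rosuvastatin, herbs) omits amiodarone.
- Exclusion (10) leaves other conditions to the investigator's discretion and sets no amiodarone rule.
- No inclusion criterion in Section 4.2 mentions the drug.

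The 60-day window therefore appears nowhere in the eligibility list.

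**Subjects still exposed.** Thirty enrolled plus one to come is 31; 1/31 = 3.2% is the most that can be affected prospectively. The documents give no prevalence of amiodarone use, so no expected count can be calculated.

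**Side check on recording.** Section 5.2 also says "Concomitant medications taken within 30 days prior to screening will be recorded in the source documents". If enrollment falls d days after screening, that record reaches back d + 30 days before enrollment, so it falls short of 60 by max(0, 30 − d): 23 days at d = 7, 16 at d = 14, 9 at d = 21, and 0 at d = 30 or 42. The values of d are illustrative. The shortfall applies to this recording rule only, not to the open-ended medication history in Section 6.10.2. The mismatch between 4.3 and 5.2 does not depend on it.

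**The case against.** The strongest reply is that the safeguard is already in the protocol. Section 5.2 prohibits amiodarone for 60 days in its own right, exclusion (8) does not repeal that, and Section 10.1.9 holds the investigator to the whole protocol. Because (8) names no drugs, anyone applying it must open Section 5.2, where the 60-day rule directly follows the general 21-day sentence and is repeated in a footnote attached to the amiodarone entry. There is only one site, so readings cannot diverge between centers, and exclusion (10) offers a further, discretionary stop. The unlimited medication history also means that past amiodarone use can come to light.

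Most of this stands, and it keeps the point minor: wrongful enrollment is possible, not likely. It does not remove the contradiction. The reference to Section 5.2 identifies which drugs are meant; the criterion then prints its own time limit, and for amiodarone that limit is wrong. At best the reader meets two limits for one drug and has to choose.

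The objection is also right that the recording rule is not an eligibility look-back, and that the 39 days measure a difference in text, not a risk.

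**Conclusion.** The inconsistency is real and minor. For amiodarone, exclusion (8) covers 21 of the 60 days that Section 5.2 prohibits and misses days 22 to 60. The intended rule is not in doubt, since Section 5.2 states it twice; the criterion was not made to match it. The practical reach is at most the one subject still to be enrolled, and then only if that person stopped amiodarone within the 39-day gap and the site overlooked Section 5.2. This conclusion rests on reading the 21 days in (8) as a limit on every drug it refers to, which is its plain sense, and on the enrollment count in Section 4.1.

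**What to change.** Amend the time limit in exclusion (8) to read: within 21 days (60 days for amiodarone) of the enrollment visit. The uncovered interval then falls from 39 days to 0, and Sections 4.3 and 5.2 agree. As a secondary step, have the medication history in Section 6.10.2 ask specifically about amiodarone in the 60 days before enrollment, because no passage now directs the site to look back that far.

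The cost is one parenthesis and one question in a history already taken, with no added visit, sample or analysis. The change should be made before the remaining subject is enrolled; if that enrollment has already happened, it is still worth making for consistency.

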# INVESTIGATIONAL MEDICINAL PRODUCTS

## Description and Handling of LDV/SOF

### Formulation

LDV/SOF tablets are orange, diamond-shaped, film-coated tablets containing 90 mg of LDV and 400 mg of SOF. The tablets are debossed with “GSI” on one side and “7985” on the other side. The LDV/SOF tablets contain the following inactive ingredients: lactose monohydrate, copovidone, microcrystalline cellulose, croscarmellose sodium, colloidal silicon dioxide, magnesium stearate, polyvinyl alcohol, titanium dioxide, talc, polyethylene glycol, FD&C yellow # 6/sunset yellow FCF aluminium lake.

### Packaging and Labeling

LDV/SOF tablets are packaged in white, high-density polyethylene (HDPE) bottles. Each bottle contains 30 tablets, a silica gel desiccant canister or sachet and polyester packing material. Each bottle is enclosed with a white, continuous thread, child‑resistant screw cap with an induction-sealed, aluminum‑faced liner.

All labels for LDV/SOF bottles to be distributed to centers in the US shall be labeled to meet all applicable requirements of the US Food and Drug Administration (FDA) and/or other local regulations as applicable.

Sufficient quantities of LDV/SOF tablets to complete the entire study will be shipped to the investigator or qualified designee from Gilead Sciences Materials & Logistics (or its designee).

### Storage and Handling

LDV/SOF bottles will be stored at controlled room temperature until required for administration. Controlled room temperature is defined as 25 °C (77 °F); excursions are permitted between 15 °C and 30 °C (59 °F to 86 °F).

All drug products will be stored in a securely locked area, accessible only to authorized site personnel. To ensure the stability of the study drug and to ensure proper product identification, the drug product will not be stored in a container other than the container in which they are supplied. Consideration will be given to handling, preparation, and disposal through measures that minimize drug contact with the body. Appropriate precautions will be followed to avoid direct eye contact or exposure through inhalation when handling LDV/SOF.

LDV/SOF pills will be repackaged according to defined standard operating procedures. Study pills will be transferred to WisePill containers in our on-site pharmacy only once a subject has arrived for a study visit. The pills will be transferred by study clinicians using gloves and designated pill tongs. Pills will be double counted to assure that there are no errors in the pill dispensation.

### Dosage and Administration of LDV/SOF

LDV/SOF tablet is to be administered once daily with or without food. Each subject will be instructed to maintain approximately the same daily dosing interval between study drug doses.

For missed dose(s) of study drug, subjects will be instructed to take the missed dose(s) of study drug as soon as possible during the same day. Subjects will be cautioned never to double the next dose with a missed dose of study drug under any circumstances.

mDOT study participants will choose a daily 3 hour “window” between 8:00AM–4:00PM in which they are expected to arrive at the study site to receive their daily dose of LDV/SOF. Subjects who have not arrived at the study site 2 hours into their designated “window” will receive one reminder (via phone call, text or email, based on subject preference). If a subject misses a daily visit, s/he will be advised to come to the study site as early as possible the following day. If the subject arrives within 18 hours of his/her designated dispensing time, a dose of LDV/SOF will be dispensed and the subject will be told s/he can return the same day for an additional dose at a minimum of 8 hours after the off-schedule dose was dispensed. In this case, the subject would resume his/her standard schedule the subsequent day.

Study staff will help subjects arrange a personal automated reminder message via their own phone, email account, or other device/service as a daily reminder to take medication (unobserved arm) or come to the study site (mDOT).

In the event that a subject in either arm anticipates missing an upcoming visit, protocol will allow for the subject to receive tablets up to 7 days beyond their planned dispensing dose.

In the event of lost or stolen medication, subjects can receive up to a maximum of 7 replacement tablets.

In the event that a subject in either arm is unable to attend study visits (due to hospitalization, detainment, or incarceration), protocol will allow for study staff to deliver medication to subject whenever possible. In such a case, subjects would receive up to 7 tablets of LDV/SOF per drop-off for unobserved daily dosing regardless of study arm.

Medication for unobserved dosing will always be dispensed in a Wisepill container unless not permitted by the facility in which subject resides.

## Prior and Concomitant Medications

Concomitant medications taken within 30 days prior to screening will be recorded in the source documents and case report form(s) (CRFs).

Concomitant use of certain medications or herbal/natural supplements (inhibitors or inducers of drug transporters i.e., P‑gp) with study drug may result in PK interactions increasing or decreasing exposure to study drug.  Examples of representative medications which are prohibited from 21 days prior to enrollment through the end of treatment are listed below. The use of amiodarone is prohibited from **60 days prior to enrollment** through the end of treatment. Participants will be advised to avoid selected medications until 21 days after the end of treatment (e.g. digoxin and rosuvastatin)

Table 5‑1. Concomitant Medications Disallowed or to be used with Caution

| Drug Class | Agents Disallowed | Use with Caution |
| --- | --- | --- |
| Acid Reducing Agents^a^ |  | Proton- Pump Inhibitors, H2‑Receptor Antagonists, Antacids |
| Anticonvulsants^b^ | Phenobarbital, Phenytoin, Carbamazepine, Oxcarbazepine |  |
| Antimycobacterials^b^ | Rifabutin, Rifapentine, Rifampin |  |
| Cardiac Medications | Amiodarone^c^ | Digoxin^d^ |
| Herbal/Natural Supplements^b^ | St. John’s Wort, Echinaccea, Milk thistle (i.e., silymarin), Chinese herb sho-saiko-to (or Xiao-Shai-Hu-Tang) |  |
| HMG-CoA Reductase Inhibitors^e^ | Rosuvastatin |  |

a It is recommended to separate antacid and LDV/SOF administration by 4 hours. H2-receptor antagonists may be administered simultaneously with or staggered from LDV/SOF at a dose that does not exceed doses comparable to famotidine 40 mg twice daily. Proton-pump inhibitor doses comparable to omeprazole 20 mg can be administered simultaneously with LDV/SOF. Proton-pump inhibitors should not be taken before LDV/SOF.

b May result in a decrease in the concentrations of study drug.

c May result in symptomatic bradycardia. Mechanism is not currently known. The use of amiodarone is prohibited from 60 days prior to Baseline/Day 1 through the end of treatment.

d May result in an increase in the concentration of study drug and/or concomitant medications. Co-administration of LDV/SOF with digoxin may increase the concentration of digoxin. Caution is warranted and therapeutic concentration monitoring of digoxin is recommended when co-administered with LDV/SOF.

e Use with study drug may result in an increase in the concentration of rosuvastatin. Monitor for signs and symptoms of muscle weakness or myopathy, including rhabdomyolysis.

Medications for disease conditions **excluded** from the protocol (e.g., active cancer, organ transplantation) are not listed under this Concomitant Medication section and are disallowed in the study.

## Study Drug Adherence

mDOT: Subjects will be observed taking LDV/SOF on a daily basis Monday through Friday. Two take-home tablets (doses for Saturday and Sunday) will be dispensed on Friday and will be monitored by the use of a Wise Pill Dispenser, a device currently used in our other trials, which allows for real-time transmission of opening data to estimate medication adherence. Wise Pill Dispensers have been shown to be reliable for real time monitoring of medication adherence, even in resource-limited settings.

Unobserved dosing: Subjects will be provided 7 tablets of LDV/SOF once weekly to take home in a WisePill Dispenser. Medication compliance of study drug will be assessed at every post-enrollment visit through weekly pill counts conducted by study staff. The pill count will take place in the on-site pharmacy and will occur prior to that week’s pill dispensation. If medication compliance is low, study staff will offer basic medication adherence advice to the subject.

## Accountability for Study Drug

The investigator is responsible for ensuring adequate accountability of all used and unused study drug bottles. This includes acknowledgement of receipt of each shipment of study drug (quantity and condition).

LDV/SOF accountability records will:

- Record the date received and quantity of study drug shipment
- Record the date, subject number, subject initials, the study drug bottle number dispensed
- Record the date, quantity of used and unused study drug returned, along with the initials of the person recording the information.

Subjects will be instructed to bring back all study drug at every post‑enrollment study visit through the end of treatment.

### Investigational Medicinal Product Return or Disposal

Please refer to Section 10.1.7 for Investigational Medicinal Product Accountability and Return.

# STUDY PROCEDURES

The study procedures to be conducted for each subject enrolled in the study are presented in tabular form in Appendix  and described in the text that follows. Additional information is provided in the study procedures manual.

The investigator will document any deviation from protocol procedures and notify appropriate regulatory authorities (e.g., IRB, DSMB, NIH, and/or Gilead).

## Subject Enrollment and Treatment Assignment

Screening and on-treatment visits will occur at screening visits 1 and 2, enrollment, and weeks 1-8. Post-treatment visits will be scheduled at weeks 1, 12 and 36 after the date of last administration of study drug.

All enrolled subjects will complete week 8 or early termination, and post-treatment weeks 1, 12 and 36 visits regardless of the treatment duration.

## Pretreatment Assessments

### Screening Visits

Subjects will be screened within 30 days of enrollment to determine eligibility for participation in the study. The screening window can be extended to 42 days in exceptional circumstances. Subjects meeting all of the inclusion criteria and none of the exclusion criteria will return to the clinic within 30 days after screening for enrollment into the study.

After consent is obtained and eligibility is determined, screening assessments (split between two visits) will include medical history and physical examination (including weight and height), review of systems, vital signs, concomitant medications, CBC with diff/CMP, PT/INR, HBsAg, HCV RNA, HCV genotype and sub-type (or lab documentation during period of diagnosis of chronic HCV), urine drug screen, HIV Ag/Ab test, and stored sample for potential HCV sequence analysis.

Subjects will be compensated $15 for screen 1 and $15 for screen 2.

### Enrollment Visit

Enrollment tests and procedures will be completed prior to enrollment and dosing/dispensing of study drug.

Enrollment visit will include a urine drug screen, urine β‑hCG (females of childbearing potential only), vital signs, randomization to study arm, motivational interviewing–based counseling pertaining to risk reduction and medication adherence, administration of the Audio Computer Assisted Self Interview (ACASI), and medication dispensation (unobserved dosing) or first directly observed dosing (mDOT).

Subjects will be randomized 2:1 to mDOT (n=20) or unobserved dosing (n=10) using permuted blocks of randomly selected sizes 2 and 4 generated using a STATA computer program. Staff members who have no contact with study participants will enclose and seal treatment allocation cards in sequentially numbered opaque envelopes to correspond with the randomization sequence. As a participant is enrolled, the envelope that corresponds with their sequence will be opened to reveal their randomized treatment condition.

mDOT subjects will receive a 10-trip Muni card to cover weekly round-trip transportation to study site and the unobserved dosing arm will receive a weekly two-trip Muni card to cover round-trip transportation to study site. These cards will be dispensed at weekly visits only so as to avoid directly compensating participants for attending daily visits.

Subjects will be compensated $20 for the enrollment visit.

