| Target Population: | Hepatitis C virus (HCV), Genotype 1 infected adults |
| Duration of Treatment: | Subjects will be treated for 8 weeks |
| Objectives: | The primary objectives of this study are as follows:   1. To assess the feasibility of treating persons who actively inject drugs (PWIDs) for HCV with Ledipasvir/Sofosbuvir Fixed-Dose Combination (LDV/SOF) by modified directly observed therapy (mDOT) versus unobserved dosing, with motivational interviewing (MI) adherence counseling, as measured by recruitment and retention rates, overall and by arm. 2. To evaluate the acceptability of mDOT versus unobserved dosing, with MI adherence counseling, among PWIDs treated with LDV/SOF, as determined by mDOT and MI participation rates, medication adherence rates and the proportion of subjects that complete therapy, overall and by arm. 3. To assess through in-depth, semi-structured qualitative interviews, the challenges required for mDOT and unobserved dosing, and identify key factors affecting treatment adherence to LDV/SOF for PWIDs.   The exploratory objectives of this study are as follows:   1. To assess end-of-treatment response and sustained virologic response (SVR), as determined by the proportion with undetectable HCV RNA at week 8 and post-treatment week 12, by arm. 2. To assess adherence to treatment by SOF metabolite levels, by arm, as needed based on SVR rates and medication adherence data. 3. To assess drug use behaviors before and after HCV treatment. 4. To assess HCV relapse and reinfection at post-treatment week 36 among participants achieving SVR. 5. To evaluate demographic, behavioral and HCV strain correlates of adherence and SVR. 6. To characterize the social and injector networks of participants in preparation for a subsequent full TasP trial. |
| Study Design: | Thirty subjects will be enrolled 2-to-1 in one of the following two treatment arms:  **Group 1:** Modified Directly Observed Therapy (N=20)   - LDV/SOF tablet (LDV 90mg/SOF 400mg) observed daily dosing (modified for non-observed Saturday and Sunday dosing) for 8 weeks   **Group 2:** Unobserved Dosing (N=10)   - LDV/SOF tablet (LDV 90mg/SOF 400mg) provided weekly (7 tablets) for unobserved daily dosing for 8 weeks |

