## Sample Size

**Sample size justification:** The sample of 30 will provide typical precision for a pilot study of feasibility and acceptability outcomes. Specifically, we will be able to estimate the mean of continuous outcomes within margins of sampling error (MSEs; half-widths of 95% confidence intervals) of 0.37 standard deviations (SD) overall, and 0.55 SDs within arm; percentages will be estimated within MSEs of 11-18 points overall, and 15-25 points within arm, depending on the sample value. In designing the full-scale trial, these exploratory results will be cautiously interpreted in the light of confidence intervals, plausibility, and prior results.

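### The stated block sizes of 2 and 4 are incompatible with the stated 2:1 allocation (20 and 10); the protocol needs to state the scheme actually used

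*Protocol*

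**What the plan says.** The allocation rule is under Enrollment Visit (6.2.2): subjects are "randomized 2:1 to mDOT (n=20) or unobserved dosing (n=10) using permuted blocks of randomly selected sizes 2 and 4". The list comes from a Stata program, and assignments are concealed in sealed, sequentially numbered opaque envelopes.

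The Study Design row of the Synopsis gives the same ratio: "Thirty subjects will be enrolled 2-to-1 in one of the following two treatment arms", with N=20 for mDOT and N=10 for unobserved dosing. The block sizes appear only under Enrollment Visit. Nowhere does the protocol say how many places in a block belong to each arm.

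Sample Size (9.7) and the Synopsis give the expected precision. For means it is a half-width "of 0.37 standard deviations (SD) overall, and 0.55 SDs within arm". For proportions, "percentages will be estimated within MSEs of 11-18 points overall, and 15-25 points within arm". A single within-arm figure is given for both arms, although the arms are planned at different sizes.

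Number of Subjects and Subject Selection (4.1) reports that thirty subjects have already been enrolled, so a randomisation list exists and can be inspected.

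**The concern.** In a permuted block design, each complete block holds the arms in the target ratio. Here one sentence fixes both the ratio and the block sizes, and they do not fit together, so at least one is misstated. The text does not show which.

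The between-arm analyses depend on this rule. Analysis Conventions (9.2) commits to intention-to-treat comparisons, and Data Analysis (9.5) specifies Fisher's exact, Wilcoxon, log-rank and GEE comparisons by arm. A reader cannot reproduce the allocation from the protocol or tell which arm sizes to expect, and a report that copies the sentence will carry the contradiction forward. The within-arm precision is also affected, because it depends on the same arm sizes.

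**Working it through.** **Inputs.** Ratio 2:1, arms of 20 and 10, and block sizes 2 and 4 (Enrollment Visit; ratio and arm sizes also in the Synopsis). Total of 30 (Number of Subjects and Subject Selection). Precision of 0.37 SD and 11 to 18 points overall, 0.55 SD and 15 to 25 points within arm (Sample Size).

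**Step 1: can a block of 2 or 4 carry 2:1?** A block of size b needs 2b/3 mDOT and b/3 unobserved places.

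| Block size | mDOT places | Unobserved places | Whole numbers? |
|---|---|---|---|
| 2 | 1.33 | 0.67 | no |
| 4 | 2.67 | 1.33 | no |
| 3 | 2 | 1 | yes |
| 6 | 4 | 2 | yes |

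**Step 2: ordinary balanced blocks (1+1 and 2+2).** Every complete block is half mDOT. In a list cut at 30, either all blocks are complete (15:15), or the first 28 places hold 14 mDOT and the last two come from an unfinished block of 4, adding 0 to 2. The range is therefore 14 to 16. In 20,000 simulated lists, 89.1% gave 15, the rest gave 14 or 16, and none gave 20.

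**Step 3: uneven blocks.** Let x be the number of complete blocks of 2 and y the number of complete blocks of 4, with 2x + 4y = 30, so x = 15 − 2y.
- 1+1 with 3+1: x + 3y = 20 gives 15 + y = 20, so y = 5 and x = 5.
- 2+0 with 2+2: 2x + 2y = 20 gives 30 − 2y = 20, so y = 5 and x = 5.

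Both mixtures can reach 20:10, but with complete blocks only when there are exactly five of each size. With the two sizes chosen at random and the list cut at 30, the 1+1/3+1 mixture gave 20:10 in about 36% of 20,000 simulated lists, with 16 to 23 mDOT overall. Its blocks are 1:1 or 3:1, never 2:1.

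**Step 4: which arm size does the stated precision imply?** Half-width for a mean in SD units: t(0.975, n − 1)/√n. Half-width for a percentage: 1.96 × √(p(1 − p)/n), taken at p = 0.1 and p = 0.5. That range of p is an assumption, chosen because it reproduces the overall figures.

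| n | Mean (SD) | Percentage (points) | Compared with the protocol |
|---|---|---|---|
| 30 | 0.373 | 10.7 to 17.9 | matches overall: 0.37; 11 to 18 |
| 15 | 0.554 | 15.2 to 25.3 | matches within arm: 0.55; 15 to 25 |
| 20 | 0.468 | 13.1 to 21.9 | no match |
| 10 | 0.715 | 18.6 to 31.0 | no match |

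The overall row confirms the formulas. The within-arm figures are those of a 15:15 split.

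**Step 5: what would fit 2:1?** Blocks of 3 (2+1) and 6 (4+2) carry 2:1 exactly. If the sizes are random and the list is simply cut at 30, the last block may be incomplete: 20:10 then occurs in about 87% of simulated lists, and 19:11 or 21:9 in the rest. A list that ends on a complete block at 30 gives exactly 20:10.

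**The case against.** The strongest defence is that this may be a wording slip and the allocation itself sound. The ratio and arm sizes appear in two places and the block sizes in only one, so the block sizes may simply be wrong. The figures 2 and 4 might even count the mDOT places in blocks of 3 and 6, although the text calls them sizes. Any randomly generated, concealed sequence still randomises. The primary endpoints include overall measures that do not depend on arm, and the protocol says that the exploratory results will be interpreted cautiously. All of this stands. It limits the consequences but does not reconcile the sentence.

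The documents do not support several stronger readings that a reader might infer:
- *The randomisation was impossible.* Step 3 shows two uneven mixtures that can reach 20:10. What is shown is incompatibility under the usual meaning of permuted blocks.
- *Participants were placed in the wrong arm, or the chance of mDOT varied from block to block.* Both presuppose a particular scheme. The realised split and the list are not shown. Even a varying chance would confound the comparison only if outcomes also drifted over enrolment, and nothing here shows that.
- *The thirty-first participant was assigned outside the random sequence.* The protocol does say that "Since there is enough study drug to treat someone, an extra study subject will be enrolled", but the same sentence places that person under the same protocol rules as everyone before. The length of the list is not stated.
- *The trial was designed as 1:1.* The precision figures fit that, but no section says so.

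**Conclusion.** The point holds as an internal inconsistency in the protocol. Blocks of 2 and 4 cannot carry 2:1. In their ordinary balanced form they give 14 to 16 mDOT among 30, against the stated 20. Uneven blocks could give 20:10, but none is described, and with random sizes the split would not be guaranteed.

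The within-arm precision makes an isolated typing error less likely, because it too fits 15 per arm. If the arms are 20 and 10, the stated 0.55 SD should be about 0.47 SD for mDOT and 0.72 SD for unobserved dosing. The stated 15 to 25 points should be about 13 to 22 and 19 to 31.

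The conclusion assumes that each complete permuted block carries the allocation ratio. The precision check also assumes t-based intervals for means and normal-approximation intervals for percentages between 10% and 50%. It concerns what the protocol specifies; whether the actual allocation was sound cannot be judged from the document.

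**What to change.** Check the stored Stata program and the envelope list, and state the scheme actually used.

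- If allocation was 2:1, correct the block sizes under Enrollment Visit to the multiples of 3 that were used (for example 3 and 6). If exactly 20:10 was required, say that the list ended on a complete block.
- If blocks of 2 and 4 were really used, state their composition and correct the ratio and arm sizes under Enrollment Visit and in the Synopsis.
- In either case, restate the within-arm precision under Sample Size and in the Synopsis for the true arm sizes, giving each arm its own figure if they differ.

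The cost is one look at an existing file, a short recalculation and a wording amendment. No new data are needed.
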